#### Aim 2 (survivor cohort)

To determine the correlation of currently available biomarkers that can be detected in the serum of cancer survivors with imaging parameters of cardiac remodeling or dysfunction.

In order to determine which biomarkers correlate with remodeling and sub-clinical dysfunction in survivors (>3 years from anthracycline chemotherapy), the same panel of biomarkers being assessed in the acute cohort samples will be evaluated. Serum will be collected from the Survivor Cohort concurrent with study echocardiograms at baseline, 1 year and 2 years (Fig. 2). Cases will be defined as patients in the Survivor Cohort demonstrating evidence of cardiac remodeling, EF < 55% (or a drop in EF of ≥10%) or CHF at any of the three study visits. The panel of biomarkers will be evaluated using the standardized methodology described above for the acute cohort.

### CORE 3: Cardiac imaging

The Cardiac Imaging Core will focus on the evaluation of new echocardiographic and CMR imaging techniques aimed at early identification of cardiac damage after anthracycline exposure. It will investigate whether changes in cardiac function immediately after anthracycline administration predict which patients will develop progressive cardiac dysfunction over time, and it will explore disease progression through the longitudinal evaluation of innovative echocardiographic parameters of remodeling and dysfunction in CCS exposed to anthracyclines. The Cardiac Imaging Core will also assess CMR markers of discrete as well as diffuse fibrotic myocardial remodeling late after anthracycline exposure and their relationship with diastolic and systolic ventricular function in a subset of eligible patients.

#### Aim 1 (acute cohort)

The core will determine whether reduced myocardial strain measurements are observed after acute anthracycline exposure and whether these changes in strain parameters predict the occurrence of adverse cardiac remodeling (as measured by changes in LV dimension and wall thickness) or dysfunction (as measured by change in ejection fraction from baseline to 12 months after therapy).

A baseline echocardiogram will be completed prior to commencing cancer therapy using a standardized functional protocol (Additional file 1). The protocol will be repeated prior to each anthracycline administration (which varies depending on each patient’s cancer treatment protocol), and at 12 months after the last dose of anthracycline chemotherapy, as outlined in Fig. 1. All images will be sent electronically to the imaging core laboratory (The Hospital for Sick Children) for centralized analysis. To standardize image acquisition at the different sites, training of the individual sonographers was provided by the core laboratory. Based on M-mode and 2-D echocardiography, LVEF by biplane Simpson’s, LVPWT and LV TDR z-score will be measured and calculated as recommended by the paediatric quantification guidelines issued by the American Society of Echocardiography [35]. Speckle tracking echocardiography is used to measure strain measurements as described by Koopman et al. [36]. Mean circumferential strain will be calculated from the basal short axis views. Circumferential strain measurements obtained in 6 segments will be averaged. Mean longitudinal strain measurements will be obtained from the apical 4-chamber view. Mean values in 6 segments will be averaged. Secondary imaging parameters including diastolic function parameters, tissue Doppler measurements and other myocardial deformation measurements will also be obtained. These will be analyzed to evaluate their usefulness for the early detection of myocardial dysfunction.

#### Aim 2 (survivor cohort)

The core will identify a sub-group of long-term survivors of childhood cancer with early signs of cardiac dysfunction, and describe the relationship of these parameters to cardiac remodeling parameters and biomarkers of cardiac damage. The trajectory of early dysfunction and remodeling over time will be examined in order to define a cardiac phenotype of early damage that can be a target of future intervention studies.

All patients enrolled in the Survivor Cohort will undergo an echocardiogram at baseline, 12 and 24 months (Fig. 2). At each of the three time points, LVPWT, TDR, and mean circumferential and longitudinal strain measurements will be performed. Subclinical dysfunction will be defined as a mean circumferential strain measurement at the basal level of the heart > − 15% or mean longitudinal strain > − 18%. The proportion of patients with evidence of sub-clinical dysfunction (assessed by strain), global dysfunction (EF < 55% or CHF) or remodeling (assessed by LVPWT, TDR) will be ascertained at each time point, and the rate of change in each parameter will be assessed over time The relationship between the remodeling parameters and strain parameters and the temporal relationship between changes in these parameters will be studied.

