**Methods:**

This is a prospective longitudinal cohort study that recruited two cohorts of pediatric cancer patients at six participating centres: (1) an Acute Cohort of children newly diagnosed with cancer prior to starting anthracycline therapy (*n* = 307); and (2) a Survivor Cohort of long-term survivors of childhood cancer with past exposure to anthracycline (*n* = 818). The study team consists of three collaborative cores. The *Genomics Core* is identifying genomic variations in anthracycline metabolism and in myocardial response to injury that predispose children to treatment-related cardiac toxicity. The *Biomarker Core* is identifying existing and novel biomarkers that allow for early diagnosis and prognosis of anthracycline-induced cardiac toxicity. The *﻿Imaging Core* is identifying echocardiographic and cardiac magnetic resonance (CMR) imaging parameters that correspond to early signs of cardiac dysfunction and remodeling and precede global dysfunction and clinical symptoms. The data generated by the cores will be combined to create an integrated *risk-prediction model* aimed at more accurate identification of children who are most susceptible to anthracycline toxicity.

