**Fig. 1 Fig1:**
[figure not shown]
Data and specimen acquisition from the Acute Cohort. BIOMKR: Serum for biomarkers, ECHO: Echocardiogram, DNA: Blood or saliva for DNA, CLIN: Gather baseline clinical data

**Table 1 Tab1:** Inclusion and exclusion criteria by cohort

	Inclusion criteria	Exclusion criteria
Acute Cohort	1. Aged <18 years at time of cancer diagnosis; 2. Diagnosed with a new malignancy; 3. Cancer treatment plan will require therapy with ≥1 dose of an anthracycline chemotherapy 4. Pre-anthracycline; echocardiograms to occur at the recruiting site; 5. Normal cardiac function prior to the initiation of anthracycline therapy (LVEF >55%).	1. Patients with significant congenital heart defects; 2. Patients who were previously treated with anthracycline chemotherapy or radiation to the chest.
Survivor Cohort	1. Aged <18 years at time of cancer diagnosis; 2. Previously diagnosed with cancer and currently in remission; 3. Patients whose prior treatment plan included therapy with ≥1 dose of anthracycline chemotherapy; 4. Patients who completed their final dose of anthracycline ≥3 years ago; 5. Patients who completed their final dose of a chemotherapy agent other than anthracycline ≥1 year ago; 6. Routinely followed at the recruiting site approximately every 12 months.	1. Prior allogeneic stem cell transplant; 2. Patients with significant congenital heart defects; 3. CMR: general contraindications for a contrast enhanced CMR, and patients who require anaesthesia for MRI (typically <6 years of age) will be excluded.

Family and medical history and demographics are collected at baseline. Data on concomitant medications are collected at each study visit. A blood (4-6 ml) or saliva (2 ml) sample is collected for DNA extraction and genomic analysis. Serial 2D echocardiograms are obtained at baseline, and at 12 months post-final anthracycline therapy dose. Additional echocardiograms are obtained prior to each dose of anthracycline in consenting patients. A blood sample (5-8 ml per time point) is collected prior to each dose of anthracycline therapy, and at 3 months and 12 months post the last anthracycline dose. The consent for biomarker studies is optional. In a subset of patients over 6 years of age, patients are also approached for consent for a cardiac MRI at the 12 month follow-up time point (Table 2).

**Table 2 Tab2:** Schedule of procedures/evaluations in Acute Cohort

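### Imaging Aim 2 defines subclinical dysfunction in survivors by strain alone, so survivors with EF <55% or heart failure can be counted in the early-damage group

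*Protocol article*

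**What the plan says.** In the protocol article, CORE 3 (Cardiac imaging), Aim 2 for the Survivor Cohort sets the rule: "Subclinical dysfunction will be defined as a mean circumferential strain measurement at the basal level of the heart" greater than −15%, or a mean longitudinal strain greater than −18%. Strain is negative, so a value above the cut-off means reduced deformation. The following sentence confirms that strain is the only criterion: "The proportion of patients with evidence of sub-clinical dysfunction (assessed by strain"). It then lists two other features, "global dysfunction (EF < 55% or CHF) or remodeling (assessed by LVPWT, TDR) will be ascertained at each time point".

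Aim 2 also states what the sub-group is for. Trajectories are examined "in order to define a cardiac phenotype of early damage that can be a target of future intervention studies". The abstract says that the Imaging Core seeks parameters that correspond to "early signs of cardiac dysfunction and remodeling and precede global dysfunction and clinical symptoms".

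In Table 1, the Acute Cohort must have LVEF above 55% before anthracycline. The Survivor Cohort has no such item. Its exclusions are "Prior allogeneic stem cell transplant; 2. Patients with significant congenital heart defects; 3. CMR: general contraindications for a contrast enhanced CMR", plus a need for anaesthesia for MRI.

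**The concern.** Dysfunction is subclinical only if overt dysfunction is absent. The rule as written leaves that condition out. Nothing in the Survivor criteria keeps patients with reduced EF or heart failure out of the cohort, so one survivor can carry the subclinical and the global label at the same visit.

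Two products of Aim 2 depend on the label: the proportion reported as subclinical at each time point, and the sub-group put forward as a target for later intervention studies. A group that includes symptomatic heart failure does not describe damage that comes before global dysfunction. A future trial that took its expected prevalence or its entry definition from this group would start from a mixed population.

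**Working it through.** **Definitions side by side.** Let S be abnormal strain (either cut-off) and G be global dysfunction as Aim 2 defines it (EF <55% or CHF).

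- The rule as written labels S as subclinical.
- The stated purpose, damage that precedes global dysfunction, corresponds to S without G.
- The difference is the set with both S and G.

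**Can that set contain patients?** Yes. Table 1 sets no EF or heart-failure criterion for survivors. The plan also expects such patients. Study outcomes counts reduced EF and symptomatic heart failure at any survivor time point, and the Biomarker Core's Aim 2 counts as cases those with remodeling, EF <55%, an EF drop of at least 10%, or "CHF at any of the three study visits", which include baseline. Aim 2 of the Imaging Core gives no hierarchy or exclusion rule between its categories.

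**Direction.** Every survivor with S but not G is labelled under either rule. The written rule can only add patients, and it does so as soon as one survivor with G has abnormal strain.

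**Size.** The article states no prevalence for Aim 2, so there is no figure to reproduce. For scale only, let g be the proportion with EF <55% or CHF, s the proportion of those with abnormal strain, and q the proportion with abnormal strain among the rest. All three are assumptions: g from 2% to 10%, s from 60% to 90%, q from 10% to 30%. Only the cohort size, 818 recruited (Survivor cohort section), comes from the document.

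- Overt cases carrying the label = 818 × g × s
- Labelled without overt disease = 818 × (1 − g) × q
- Overt share of the labelled group = g·s / [g·s + (1 − g)·q]
- Excess in the reported proportion = g·s

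| g | s | q | Overt and labelled | All labelled | Overt share | Proportion, written rule | Proportion, EF ≥55% and no CHF required |
|---|---|---|---|---|---|---|---|
| 2% | 60% | 30% | 10 | 250 | 3.9% | 30.6% | 29.4% |
| 5% | 60% | 20% | 25 | 180 | 13.6% | 22.0% | 19.0% |
| 5% | 90% | 20% | 37 | 192 | 19.1% | 23.5% | 19.0% |
| 10% | 90% | 10% | 74 | 147 | 50.0% | 18.0% | 9.0% |

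Third row written out: 818 × 0.05 × 0.90 = 37; 818 × 0.95 × 0.20 = 155; 37/192 = 19%. The first and last rows are the extremes of the assumed range. Across it, the excess in the reported proportion runs from 0.02 × 0.60 = 1.2 to 0.10 × 0.90 = 9.0 percentage points.

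**The case against.** The strongest reply is that the text contains no contradiction. Aim 2 reports three features, and global dysfunction has its own definition in the same sentence. A reader may take it that overt cases are identified there, and a condensed article may leave the overlap rule to a fuller document. This does not dispose of the point. The article does not leave the definition open: it gives a complete rule with cut-offs and repeats that strain decides. Read literally, that rule labels overt cases as subclinical.

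Several limits on the point do stand.

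- A reader might infer that the categories are disease stages that wrongly overlap. The article never calls them stages, ranks them or says that they exclude each other.
- A reader might infer that the label biases the strain–remodeling relationship and the order of changes. Aim 2 describes those analyses on the measured parameters and their rates of change, not on the binary label, so correcting the definition leaves them unchanged. Whether overt disease drives a cross-sectional association is a separate question, suited to a sensitivity analysis.
- It is tempting to restrict the temporal analysis to visits with preserved EF. That would drop the visits needed to see whether strain change comes before EF decline.
- Overt cases can be separated at analysis without new data, because EF and CHF status are ascertained at each time point. This makes the correction cheap; it does not make the written rule right.

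**Conclusion.** The point holds as a definitional fault in one imaging aim. The written rule allows overt dysfunction into the subclinical proportion and into the sub-group offered as the early-damage phenotype, against the core's stated purpose. The upward direction follows from the text, provided that at least one survivor with EF <55% or CHF has abnormal strain. The size does not follow from the text: the 4% to 50% share, or 10 to 74 survivors, rests wholly on assumed prevalences, and its width shows how little the article determines.

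A reader might extend the fault to the study's main results. The documents do not support that. The primary outcome in Study outcomes, the survivor case definition in the Biomarker Core and the 12-month classification in the risk-prediction section use remodeling, EF and heart failure, not strain cut-offs.

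**What to change.** - **Definition.** At each survivor visit, define subclinical dysfunction as strain beyond either cut-off AND EF ≥55% AND no CHF. This mirrors Aim 2's own definition of global dysfunction.
- **Reporting.** Give strain abnormality with and without global dysfunction separately. Keep remodeling as a cross-classified feature, so that its co-occurrence with abnormal strain, which Aim 2 studies, stays visible.
- **Analysis.** Keep all visits in the longitudinal and temporal analyses. Add, as a sensitivity analysis, the cross-sectional association of strain with remodeling and biomarkers in survivors with preserved EF.

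The cost is one sentence in the definition, one derived variable from data already collected and one added analysis. The stated subclinical proportion becomes somewhat smaller.

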#### Aim 3 (acute and survivor cohorts)

The core will determine whether markers of diffuse or discrete myocardial fibrosis by T1 mapping CMR are associated with echocardiographic parameters of cardiac dysfunction and biomarkers of collagen metabolism.

Extracellular volume fraction (ECV) and native T1 time in the myocardium are both elevated in states of extracellular matrix expansion, as in diffuse myocardial fibrosis. In a pilot study,

Sixty patients from the survivor cohort will undergo one single CMR examination at any one of their three study visits. The CMR will include ECV and T1 measurements as well as assessment of ventricular volumes and ejection fraction. Discrete myocardial scarring will be assessed by means of LGE. ECV and T1 will be correlated with echocardiographic markers of systolic and diastolic myocardial and ventricular function. In addition, patients will be grouped into those with normal and those will abnormal diastolic function, as indicated by the mitral valve inflow and pulmonary vein profiles.

### Developing a risk prediction model

To achieve the primary objective of the Acute Cohort study (identifying patients at increased risk for therapy-induced cardiac disease prior to starting or during therapy), evolution of echocardiographic parameters over the treatment duration will be modeled in linear and non-linear regression models adjusted for repeated measures through a compound symmetry covariance structure. The resulting general estimating equations (GEE) will provide an estimate of the effect of anthracyclines over time for the entire cohort and the parameter estimate (slope of change over time) for each individual patient will be used as a potential predictor of therapy-induced cardiac damage. Twelve months after their final cycle of anthracycline chemotherapy, patients will be classified as having cardiac disease or not based on evidence of remodeling or decreased EF or CHF. Potential factors associated with acute cardiac change or cardiac damage at 12 months after treatment will be sought from patient demographics (e.g. age at treatment, gender), treatment (e.g. cumulative anthracycline dose, radiation exposure), genomics, serial biomarkers and echocardiographic measurements at baseline and during follow-up. Because of the very large number of potentially associated factors (and the multiple variations in format/time points for many factors), we will have to reduce the number of candidate factors using a pre-specified algorithm. As exploratory analyses, univariate regression models using therapy-induced cardiac changes or cardiac disease at 1 year (present vs. absent) as the dependent variable, and all other collected variables as potential independent variables will be created. This will allow exploration of variables potentially associated with therapy-induced cardiac damage including assessment of collinearity, ill condition (variables with no events in one of the study groups) or amount of missing data. All variables with univariable *p*-value <0.30, excluding collinear variables, ill conditioned variables or variables with an unacceptable amount of missing data will be included in a bootstrap bagging algorithm. A total of 5000 random sub-samples will be created and for each of those, a mixed stepwise regression model will be used to obtain multivariable predictors for therapy-induced cardiac damage. The proportion of sub-samples in which a given variable is selected is called reliability. Variables with high reliability (>50%) will then be included in a multivariable regression model with backward selection of variables to obtain a final model. This algorithm significantly improves the accuracy of variable selection, reduces the probability of sampling bias and corrects for multiple comparisons better than a post-hoc analysis would. At the end of this algorithm we will be left with a limited number of associated factors, all with high reliability. Based on the reliability estimates, we will be able to determine whether the risk of therapy-induced cardiac changes or cardiac damage at 1 year after anthracycline exposure is driven by baseline measurements (including clinical, genomic, echocardiographic or biomarkers), by reaching specific milestones during anthracycline treatment, by change over time in cardiac dimension/function and biomarkers during anthracycline treatment, or by a combination of all three.

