### Acute cohort

A prospective cohort of patients newly diagnosed with cancer who received anthracycline chemotherapy has been recruited from clinics at the four pediatric participating centres (recruitment target *n* = 270; recruitment actual *n* = 307). We will assess whether genetic predictors of anthracycline susceptibility, biomarkers of early cardiac damage, and imaging parameters of acute cardiac dysfunction predict which patients will demonstrate evidence of persistent or progressive cardiac damage at the 12 months follow-up from their last cycle of anthracycline chemotherapy (See Fig. 1 for timeline of sample and data acquisition in Acute Cohort). Eligibility criteria for both cohorts are provided in Table 1.

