Procedure/Evaluation	Baseline (prior to starting anthracycline)	Study Visits prior to each anthracycline dose	3 months after completion of final anthracycline dose (± 4 weeks)	12 months after completion of final anthracycline dose (± 8 weeks)
Informed Consent/Assent	X			
Demographics	X			
Height (cm) & Weight (kg)	X	X	X	X
Concomitant Medications	X	X	X	X
Medical History	X			
Review of Medical Events	X	X	X	X
Cancer Therapy		X	X	
Echocardiogram (ECHO)	X	X^a^		X
Genetic Sample	Obtain one sample at any time point while patient is on-study^%^			
OPTIONAL Biomarker Sample	X	X	X	X

^%^For patients who will be having an allogeneic stem cell transplant, collect the genetic sample prior to the procedure

^a^ECHOs will be performed prior to each dose of anthracycline when possible. If patient/parent is not agreeable to research-only ECHOs, then they will occur only at clinically indicated time points

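### The cohort-level slope over the treatment period is called the effect of anthracyclines, but with every Acute Cohort child exposed it can only show change during anthracycline-containing treatment

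*Protocol article*

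**What the plan says.** The section on developing a risk prediction model states that "evolution of echocardiographic parameters over the treatment duration will be modeled in linear and non-linear regression models adjusted for repeated measures", with a compound symmetry covariance. It gives the resulting equations two uses. At cohort level they "will provide an estimate of the effect of anthracyclines over time for the entire cohort". At patient level, "the parameter estimate (slope of change over time) for each individual patient will be used as a potential predictor".

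On exposure, Table 1 requires of the Acute Cohort that "Cancer treatment plan will require therapy with ≥1 dose of an anthracycline chemotherapy". The Acute cohort section describes the 307 recruited children in the same way: "A prospective cohort of patients newly diagnosed with cancer who received anthracycline chemotherapy has been recruited". No unexposed group is described.

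Cumulative dose and radiation appear later in the same section, among the candidate factors for cardiac change or damage: "treatment (e.g. cumulative anthracycline dose, radiation exposure", and so on. The text does not make them terms of the GEE.

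**The concern.** The sentence gives a time trend a causal label. In a cohort where everyone is exposed, a trend over the treatment period is a before-after comparison without a control. Whatever else changes over that period goes into the same slope.

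The article itself points to such influences. It names radiation as a treatment factor, and the Background lists radiation to a field involving the heart as an established cardiac risk factor. Prior chest radiation is an exclusion for this cohort, so any chest radiation in these children comes after entry. Concomitant medications are recorded at every visit, and a footnote to Table 2 foresees allogeneic transplant for some patients.

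At stake is one published number. If the slope is reported under the stated label, readers will take a change with several possible causes as the size of anthracycline toxicity, which is the subject of the study.

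**Working it through.** The article gives no figure for this effect, so there is none to reproduce. The check asks what the described parameter identifies.

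**Inputs from the article**
- Exposure: all 307 children (Table 1, inclusion 3; Acute cohort section).
- Model: echocardiographic parameter on time, repeated measures, compound symmetry. The only parameter named is the slope over time.
- Schedule: Cardiac imaging, Aim 1 says the pre-dose echocardiograms follow each patient's treatment protocol.

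**Step 1. Meaning of the slope.** Let *a* be the change per unit time due to anthracycline and *b* the change due to everything else over the same period. With all children exposed,

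E(Y) = β0 + (a + b)·t.

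The GEE estimates β1 = a + b. The covariance structure affects precision, not this meaning. The pre-anthracycline baseline does not help, because the mean change from baseline to time t is also (a + b)·t. Z-scores for wall thickness and thickness-to-dimension ratio deal with much of growth, but not with concurrent treatment.

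**Step 2. Can a and b be separated on time alone?** Giving each its own time column yields a design with columns 1, t, t. Its rank is 2 for 3 columns, so they cannot.

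**Step 3. Illustration.** Assumed, not from the article: 5 echocardiograms per child, a total ejection fraction slope of -1 point per visit, and between-child and residual SDs of 3 each. With n = 307, an exchangeable GEE and 20 replicates:

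| a | b | Share due to anthracycline | Mean fitted slope | Mean SE |
|---|---|---|---|---|
| -1 | 0 | 100% | -0.99 | 0.05 |
| -0.5 | -0.5 | 50% | -1.01 | 0.05 |
| 0 | -1 | 0% | -1.01 | 0.05 |

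The simulation error of each mean is about 0.054/√20 = 0.012, so the rows do not differ beyond noise. They could not, since the data depend only on a + b. The table restates Step 1 and says nothing about the true split in this cohort.

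**Step 4. What could separate them.** Steps 2 and 3 use time alone. Because dosing schedules vary, cumulative dose d up to each echocardiogram is not a fixed function of time. A model E(Y) = β0 + β1·t + β2·d can then estimate β2. That contrast exists in the data, but the described slope does not use it. It is not clean either: dose is set by the treatment protocol, so it varies together with the rest of the regimen.

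**The case against.** The strongest reply is that nothing downstream needs a causal reading. The section is about prediction, and none of the four study aims is to estimate the size of an anthracycline effect. A patient's own slope can predict later damage whatever caused it. Apart from the one clause, the section attributes outcomes to therapy in general. All of this stands, and it limits the consequence. It does not make the clause correct.

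A second reply is that a condensed article leaves the covariate list to a fuller document, and that time might be indexed by dose visit, since Table 2 has a column for "Study Visits prior to each anthracycline dose". The missing list is indeed no finding. But the article makes a positive statement about what the slope estimates, and names only a slope over time. Counting time in dose visits would bring the axis closer to exposure, but other treatment given between those visits would still move along it.

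Several stronger readings are tempting but not supported:
- **Imaging Aim 1 would be answered wrongly.** That aim asks "whether reduced myocardial strain measurements are observed after acute anthracycline exposure". This is temporal and descriptive, and a fall in strain after exposure answers it whatever the cause.
- **Any fall in function would be reported as anthracycline cardiotoxicity.** The 12-month classification is of cardiac disease present or absent, and dose and radiation are both candidate predictors.
- **Every child receives other cancer treatment.** The article shows co-exposures for some children and does not say this of all. The point does not need it.
- **A dose coefficient would isolate the drug effect.** It remains open to confounding by regimen.

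**Conclusion.** The point holds for the cohort-level statement. The slope is change over the treatment period in children who all received anthracycline, and it cannot be attributed to anthracyclines. This rests on two things the article states: universal exposure, and a slope over time as the only named parameter. If a fuller analysis plan already puts cumulative dose into this model, the statement still needs to refer to the dose term and not to the time slope.

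No size of bias can be derived. If a share s of the decline has other causes, the labelled effect is 1/(1 - s) times the true one. A reader might insert 25% or 75% and obtain 1/0.75 = 1.33 or 1/0.25 = 4, but the article supports no value of s. Other influences could also act in the opposite direction, so that the slope understates the effect.

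The use of individual slopes as predictors and the wording of Imaging Aim 1 need no change on this account. This is a correction worth making to one claim, not a flaw in the prediction strategy.

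**What to change.** 1. Replace the claim in the risk prediction section: describe the cohort slope as change during anthracycline-containing cancer treatment. This costs only wording.

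2. If an anthracycline-specific estimate is wanted, add cumulative anthracycline dose received up to each echocardiogram as a time-varying term. Keep time as a covariate, and add recorded co-treatments such as chest radiation. Report the dose coefficient as an association still subject to confounding by regimen.

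The second step changes the model, not only the text. It needs no new visits for the treatment period, because Table 2 schedules cancer therapy data at each pre-dose visit and at 3 months. That row is not marked at 12 months, so if the 12-month echocardiogram is brought into the model, the source of therapy data after month 3 has to be stated. The downside is that the dose coefficient will be less precise than the time slope, and the claim more modest.
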